### Data Management

Personal information and data for all experiments are handled by the personal information manager director of Tohoku University. Access to information requires a key that is securely kept and has limited access. These internal checks and balances ensure the security of all data and personal information. After the experimental period ends, the data will be consolidated. Any information linking data back to the participant will be discarded to ensure that the data are truly anonymous. Data destruction will not be conducted.

### Data Monitoring and Auditing

We will follow the recommended guidelines for clinical research in Japan^2^. According to the guidelines, data monitoring by a third party is unnecessary for this study because we are not providing participants with any medications, nor are we conducting surgery.

### Research Ethics Approval and Informed Consent

The Ethics Committee of Tohoku University Graduate School of Medicine approved the study protocol. They will approve the consent form. Participants will be given both an oral explanation and a written file that documents details of the study. Upon understanding, the participant will be asked to give written consent by signing the consent form. Participants might choose to withdraw from the study at any point in time. Should they choose to do so, their data would be destroyed.

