## Hypothesis

### Primary Hypotheses

Acute intervention with high-intensity physical exercise leads to significantly shorter reaction time at the Stroop task compared to intervention with low-intensity physical exercise.Acute intervention with the brain training video game Brain Age leads to significantly shorter reaction time at the Stroop task compared to intervention with the Tetris video game.Because an acute intervention of physical exercise might have a stronger effect on cognitive function than video gaming (McMorris and Hale, 2012; Bherer, 2015), the order for the other interventions with regard to the reaction time at the Stroop task is from short to long reaction time: (1) High intensity + Brain Age; (2) High intensity + Tetris; (3) Low intensity + Brain Age; and (4) Low intensity + Tetris.Acute intervention with high-intensity physical engenders stronger activations in DLPFC, VLPFC, and FPA compared to low-intensity physical exercise.Activation of R-FPA correlates with the performance (inversely with reaction time) at the Stroop task.Acute intervention with Brain Age video game leads to significantly different activation patterns from those obtained from intervention with Tetris video game, which also correlates with better performance at the Stroop task.

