### Sample Size

Calculation of the sample size is not possible because no similar study has been reported to date. Soares et al. (2016) report that the optimal sample size for adequate reliability and power in fMRI studies might be between 16 and 32 participants. Zysset et al. (2007), who also conducted an experiment with Stroop task in fMRI, respectively used 23 and 24 participants per group. We also aim to include 24 participants.

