### Cognitive Task

The color-word matching Stroop task was adopted and conducted in an event-related design (Yanagisawa et al., 2010; Hyodo et al., 2012) using software (E-Prime 2.0.10.42, E-Studio 2.0.10.147; Psychology Software Tools, Inc., Sharpsburg, PA, USA). The participant is presented with two rows of words and is instructed to decide whether the meaning of the color word in white ink in the bottom row matches the color of the word in the first row. The participants can input their choice by pressing a button with the index finger and the middle finger to give “yes” or “no” responses. The order in which the participants must answer “yes” or “no” is randomized. The assignment, whether the index finger is “yes” and the middle finger is “no” or vice versa, is counterbalanced across participants and across the two halves of one experimental session. The correct answer rate assigned to yes and no is 50% each. The correct answer rate and reaction time are also measured.

Trials of two types are compared in the Stroop task. For the congruent trials, the top row were words “RED,” “BLUE,” “YELLOW” or “WHITE” printed in their respective ink and the bottom row contains the words “RED,” “BLUE,” “YELLOW” or “WHITE” in black ink. For the incongruent trials, the top row includes the words “RED,” “BLUE,” “YELLOW” or “WHITE” in an incongruent color, whereas the bottom row is the same such as in the congruent trials. Each experimental session consists of two halves separated by a small break, each with 48 congruent and 48 incongruent trials that are presented in random order. Consequently, the total number is 192 trials (96 congruent and 96 incongruent trials). All word stimuli are presented in Japanese. To prevent the participants from particularly addressing the bottom row and blurring out the top row, the top row is presented 300 ms earlier than the bottom row. Visual attention should shift automatically to the top row then (Zysset et al., 2007; Hyodo et al., 2012). The stimulus is presented on the screen for 2 s. To avoid prediction of the timing of the subsequent trial, each trial is separated by an interstimulus interval showing a fixation cross for 2 (96 trials), 4 (72 trials) or 6 s (24 trials). The whole session lasts around 16.8 min plus the brief pause between the two halves.

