### Randomization

We conduct four interventions per participant and use a Latin square counterbalancing that sums up to four sequences in all (see CONSORT flowchart). First, it would be wasteful for organizational purposes and costs for MRI to cover every possible sequence (24 in total) because it would necessitate 24 separate intervention sessions for each participant. Second, the risk of having a bias because of carry-over effects might be higher when two high-intensity bouts follow each other than with two low-intensity bouts because results demonstrated that biomarker for cognitive improvement (e.g., brain-derived neurotrophic factor, BDNF) might still influence the performance, even after 7 days (Skriver et al., 2014). It is not confirmed, but by separating the two high-intensity bouts from each other, it might decrease this bias. To make it more homogeneous, high-intensity and low-intensity bouts are conducted in an alternating fashion.

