### Stroop Task Analysis

We will use R (R Core Team, 2018) and lme4 (Bates et al., 2015) to perform linear mixed effects analysis of cognitive performance in dependence of physical exercise and video gaming. For reaction time at the Stroop task, we enter physical exercise intensity (high/low), video game (Brain Age/Tetris), week (1, 2, 3, 4), congruency of the Stroop task (congruent/incongruent), age (60–70 years), and gender (male/female) as fixed effects into the model. As random effects, we have intercepts for participants, as well as by-participant random slopes for the effect of physical exercise intensity and video game. Expectations for improvement at the cognitive task also enter as fixed effects into the model and the correlation with other predictors should be checked. For the correct answer count at the Stroop task, we will use the generalized linear mixed-effects model analysis and take the same fixed and random effects as above. Visual inspection of residual plots should be checked to ascertain whether they reveal any marked deviations from homoscedasticity or normality. *P*-values are obtained from likelihood ratio tests of the full model with the effect in question against the model without the effect in question.

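### Destroying the data of everyone who withdraws discards completed sessions that the planned Stroop mixed models could use (minor; cheap to improve)

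*Protocol article*

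**What the plan says.** All references are to the protocol article.

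- Research Ethics Approval and Informed Consent: "Participants might choose to withdraw from the study at any point in time". The next sentence is "Should they choose to do so, their data would be destroyed". No exception for completed sessions is stated.
- Stroop Task Analysis: R and lme4 will be used "to perform linear mixed effects analysis of cognitive performance in dependence of physical exercise and video gaming", with participant intercepts and by-participant slopes for exercise and game. A generalized mixed model with the same effects is planned for correct answers.
- Randomization: four Latin-square sequences are used, in which "high-intensity and low-intensity bouts are conducted in an alternating fashion".
- Primary Hypotheses: the first reads "Acute intervention with high-intensity physical exercise leads to significantly shorter reaction time at the Stroop task" than the low-intensity bout.
- Sample Size: "We also aim to include 24 participants". The section says that no calculation was possible, and it gives no allowance for dropout.
- Cognitive Task: in each session, "the total number is 192 trials (96 congruent and 96 incongruent trials").

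**The concern.** The withdrawal rule and the analysis model pull in opposite directions. A mixed model accepts unequal numbers of sessions per person. In an alternating design, a person with two sessions already contributes a within-person high-versus-low difference, which is the first primary contrast. The destruction rule removes that contribution and leaves an analysis of people who did not withdraw.

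Two things are at stake. The first is precision, in a crossover of 24 people whose size rests on no power calculation. The second is possible selection: if people who respond badly to the high-intensity bout leave more often, dropping their recorded sessions tilts the comparison towards the hypothesis. If the opposite group leaves, the tilt reverses. If leaving is unrelated to response, there is no tilt.

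This is a rule that the protocol fixes, not a detail left for an analysis plan, because destroyed data cannot be restored at the analysis stage.

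**Working it through.** The plan gives no figure to reproduce, and no variance or withdrawal rate. What follows is an illustration under stated assumptions.

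**Inputs from the protocol.** 24 participants; four weekly sessions each, so 24 × 4 = 96; four sequences with alternating intensity; 192 trials per session.

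**Assumed inputs.** Six participants per sequence in a cyclic alternating square (the actual square is in a figure not shown). Residual SD σ = 40 ms per session. Participant SD τ of the exercise and game effects = 20, 40 or 60 ms. Participant intercept SD 150 ms. One, two or three people leave. Fixed effects are exercise, game and week, fitted by generalized least squares with known variances.

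**Step 1, all data.** Each person has two high and two low sessions, so the variance of one person's difference of means is τ² + σ²(1/2 + 1/2) = τ² + σ², and SE = √[(τ² + σ²)/24].
- τ = 20: √[(400 + 1,600)/24] = 9.13 ms
- τ = 40: √[(1,600 + 1,600)/24] = 11.55 ms
- τ = 60: √[(3,600 + 1,600)/24] = 14.72 ms

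**Step 2, what is destroyed.** Each person who leaves after session 2 takes away 2 × 192 = 384 trials: 384, 768 or 1,152 for one, two or three leavers.

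**Step 3, SE relative to all data.** With leavers removed, the ratio is roughly √[24/(24 − k)]: 1.022, 1.044 and 1.069 for k = 1, 2, 3. The full model gives slightly more because balance over weeks is also lost. Dividing by the ratio with two sessions kept isolates the cost of the rule from the cost of sessions that never took place.

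| Leavers after session 2 | Destroyed / all data | Two sessions kept / all data | Destroyed / kept |
|---|---|---|---|
| 1 | 1.022 | 1.009–1.011 | 1.022/1.011 to 1.022/1.009 = 1.011–1.013 |
| 2 | 1.046–1.047 | 1.017–1.022 | 1.046/1.022 to 1.047/1.017 = 1.023–1.030 |
| 3 | 1.072–1.073 | 1.025–1.032 | 1.072/1.032 to 1.073/1.025 = 1.039–1.047 |

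The exact value depends somewhat on which sequences the leavers come from.

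**Step 4, timing.** With only one session kept, the ratios to all data are 1.021–1.022, 1.044–1.045 and 1.068–1.070, almost the same as with everything destroyed. One session holds no within-person contrast, so little is recoverable. A separate calculation with different assumed variances (intercept 1.0, slopes 0.1, residual 0.5) gives a destroyed/kept increase of 0.2% to 1.6% for one leaver and 0.4% to 3.1% for two, over departures after session 1 to session 3. The order of size is the same.

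**Step 5, bias.** In simulation, leavers chosen at random produced no bias beyond simulation error, whether data were destroyed or kept. As an outer bound, the leavers were taken to be exactly those with the largest observed high-minus-low time in sessions 1–2. Destroying their data then shifted the estimate by −2.7 to −4.8 ms (one leaver), −5.0 to −8.6 ms (two) or −7.4 to −12.6 ms (three). Keeping the two sessions held it within about 0.3 ms of zero, but only because leaving was made to depend on recorded results.

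**The case against.** **The precision cost is small.** This stands. The larger increases against all data (2.2% to about 7%) include sessions that would never have taken place. The share due to the rule is the last column of the table.

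**Intolerant people are largely screened out first.** Three familiarization sessions with growing time at high intensity come before allocation, and those uncomfortable with exercising are excluded at that stage (Interventions Overview, Eligibility Criteria, Allocation and Implementation). This also stands. It makes exercise-related withdrawal less likely, though still possible, since four weekly sessions follow. The outer-bound bias figures should therefore not be read as expected bias, and nothing in the protocol suggests that leaving tracks Stroop time.

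**Destruction is a participant's right in an ethics-approved protocol.** It is a legitimate choice to offer. That does not require destruction to be automatic, and the fix keeps it available on request.

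A reader might infer more than the protocol supports:
- *The reasons for leaving are lost.* The rule does not say what counts as data, and the flowchart and consent form are not shown.
- *Tolerability is understated.* No tolerability estimate is planned, and a session stopped on the exercise-interruption criteria is not itself a withdrawal.
- *The protocol contradicts itself.* Data Management says "Data destruction will not be conducted", but in a passage about the period after the experiment, so the two statements can be read together. The differing text on how long the linking file is kept is a confidentiality matter.
- *The Borg ratings are wasted.* They serve as a stopping criterion and are not a listed outcome, so the absence of a named analysis is no error.

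**Conclusion.** The point holds as a minor one. Read as written, the rule drops every voluntary withdrawer from the primary high-versus-low comparison, including people who have already given both intensities, although the chosen models could use them. The expected loss is about 1%, 2–3% or 4–5% in the standard error of the exercise effect for one, two or three leavers after session 2. It is near zero for departures after session 1.

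These figures rest on assumed variances, an assumed square with equal allocation and an assumed number of leavers. Whether the estimate is biased, and in which direction, depends on why people leave, which the protocol cannot settle. It would be wrong to say that the result will be biased in favour of high intensity. The case for change is that the loss is avoidable and cannot be undone.

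**What to change.** Reword the withdrawal sentence in Research Ethics Approval and Informed Consent, and the consent form, along these lines: a participant who withdraws is asked whether the data collected so far may be kept in de-identified form. With agreement, the completed sessions enter the models in Stroop Task Analysis. If the participant asks for destruction, the data are destroyed and only the number of such withdrawals is reported.

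The cost is an ethics and consent-wording amendment, and a de-identified record held, with permission, about people who leave. No new measurement or model is needed. Keeping partial data does not remove every bias: it helps where leaving depends on results already recorded, not where it depends on something unrecorded.

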### Confidentiality

All participants will be given subject identification numbers to which all the data will be linked. The file records that connect each participant to their identification number will be securely kept on laboratory servers during the study. After the study is concluded, the file will be kept for 3 years and will be destroyed afterward. This study is conducted using the operating grants of the group of Tohoku University of implementation officer.

### Access to Data

As described previously, all personal information and data for the experiment are handled by the personal information manager director of Tohoku University. Access to information requires a securely kept key with limited access. These internal checks and balances ensure the security of all data and personal information.

### Dissemination Policy

Results of the study will be published formally in a journal. Participants, the public and other relevant groups will not be individually notified of the results. There is no publication restriction to note. Authorship of the study belongs to those specifically listed; no professional writer was involved. Currently, no plan exists to grant public access to the full protocol, participant-level dataset, and statistical code. For interested researchers, we have the following ideas for data sharing. For the study protocol, the current protocol article should be the full protocol. For statistical analysis, we will use open source softs and packages such as R and SPM for behavior and brain imaging analyses. We will not have any plans to use customized statistical codes. For the participants-level dataset, behavioral data will be available on Open Science Framework^3^ or will be uploaded the journal web as a supplemental information material. On the other hands, we will not share structural and functional MRI dataset. The MRI datasets will be available on requests after getting an approval of the reuse of MRI dataset from our ethical committee.

## Discussion

This study is a randomized within-subject crossover controlled trial to test the response of Stroop task performance (cognitive task for executive function) and the related brain activity using fMRI to an acute bout of high-intensity physical exercise followed by a short session with a brain training video game in physically active and cognitively healthy older adults (60–70 years). The control conditions are low intensity for physical exercise and Tetris for video gaming.

### Physical Exercise

As mentioned in the introduction, there are several variables to consider when using physical exercise as an acute intervention in order to improve cognitive abilities. To construe the outcome of acute exercise, certain variables to keep in mind include the exercise intensity (low, moderate or high), the time point at which the cognitive test is applied after the physical exercise (during, immediately after or after a brief pause), and the type of cognitive test (attention, executive functions, memory, etc.; Chang et al., 2012). Using these variables, hypotheses such as the inverted-U-shaped hypothesis (Chmura et al., 1994; McMorris et al., 2011), which predicts stronger benefits at moderate intensity than at low or high intensity, or the drive hypothesis (Chang et al., 2012), which posits higher intensity as producing better cognitive improvement, are explainable to a certain extent (Chang et al., 2012). Whereas the cognitive test is applied immediately after exercise, lower and moderate intensity are apparently more favorable for cognitive improvement than high intensity, which supports the inverted-U-shaped hypothesis. When cognitive testing is applied after a short delay from several minutes up to a few hours after the exercise, lower intensities exhibit no significant improvement. The degree of improvement shifts to higher intensities, which favors the drive hypothesis. Cognitive improvement and metabolic response seem to have their maximum effects at a delay of 11–20 min after high-intensity exercise (Chang et al., 2012). Results demonstrated that the speed at executive function tasks improves significantly after acute exercise, whereas the accuracy remains non-significant or even decreases slightly (McMorris et al., 2011; McMorris and Hale, 2012).

The mechanism behind the improvement of cognitive function after physical exercise is already widely debated. Especially after an acute intervention, it is most likely attributable to the release of neurotransmitters (Hillman et al., 2008; Skriver et al., 2014) such as BDNF (Piepmeier and Etnier, 2015), vascular endothelial growth factor (VEGF) or insulin-like growth factor 1 (IGF-1), catecholamines (McMorris and Hale, 2015), changes of cerebral blood flow (Ogoh et al., 2014), cerebral oxygenation and oxygen usage (Coetsee and Terblanche, 2017a), or arousal level (Kamijo et al., 2004). In young adults, it might be demonstrated that BDNF peaks after 15–20 min (Schmidt-Kassow et al., 2012) and right at the time when participants enter the fMRI session, which is also a reason why the physical exercise is conducted before the video gaming session.

### Video Gaming

Interventions with cognitive training or video games always aim to exert a so-called transfer effect (Hertzog et al., 2008). Transfer means to convert individual improvements, say, from a video game, to other cognitive tasks. The transfer can be divided further into near transfer, by which trainees improve on tasks that are not identical, but which are closely related to the training; with far transfer, performance is improved on non-related tasks or even on tasks in real-life situations. Video games show some difficulties in eliciting transfer effects (Green and Bavelier, 2008), even exhibiting weak to no correlation between video game experience and cognitive function (Redick et al., 2017). Nevertheless, in recent years, video games, especially action video games, have shown positive results on far transfer effects in areas such as visual spatial ability (Green and Bavelier, 2007; Green et al., 2010). However, other categories of video games show promising results in the same (Toril et al., 2016) or other cognitive functions as well (Basak et al., 2008; Oei and Patterson, 2013). Improvements in cognition related to video games tend to be shared features between the video games and real-world/cognitive task rather than generalized, non-specific transfer (Oei and Patterson, 2014). The mechanisms underlying cognitive improvement because of video games are yet to be elucidated. However, factors such as virtual environments, challenges, and reward systems might affect cognitive function (Monteiro-Junior et al., 2016). Thus, video games might present the difficulty to transfer to other cognitive challenges (Redick et al., 2017), so it can also turn out that Brain Age shows no positive results in this scenario where it is used as an acute intervention with an executive function task for older adults as participants (Ackerman et al., 2010; Owen et al., 2010). Nevertheless, it can be ascertained whether differences exist in brain activities between the conditions that might explain these circumstances.

### Combination of Physical Exercise and Video Gaming

For the combination of physical exercise and video games, animal experiments already demonstrate that there are additive improvements of cognitive functions with a combination of physical exercise and cognitive challenges (Fabel et al., 2009; Kempermann et al., 2010), but there is still a lack of data related to this topic of a combination of physical exercise and video gaming in general (Mishra et al., 2012). Some reports of studies of exergaming already exist, but the results they describe remain controversial (Ordnung et al., 2017; Stanmore et al., 2017). In older adults, dancing with a dual-task character (physical exercise and cognitive challenge) is superior on acute improvement task-switching reaction time (executive function) than comparable physical exercise alone (Kimura and Hozumi, 2012). Other studies have found no significant improvement after one session of exergaming compared to the control group (Guzmán and López-García, 2016; Monteiro-Junior et al., 2017), but have also found a reduced rate of perceived exhaustion (RPE) compared to moderate aerobic physical exercise alone (Guzmán and López-García, 2016). A recent systematic review from Zeng et al. (2017) concluded that results for exergaming used as a therapeutic tool are inconsistent, but there are no negative outcomes, so it might feasible to use for older adults (Chao et al., 2015), even with mild cognitive impairments (Hughes et al., 2014).

Because reports of the literature are scarce for many aspects of this study, e.g., acute intervention of video gaming for results at the Stroop task or for brain imaging in older adults, definite hypotheses are challenging to formulate. However, based on the remaining literature, this study should find answers to following hypotheses: an acute intervention with physical exercise might have a stronger effect on cognition than an acute intervention with video gaming (McMorris and Hale, 2012; Bherer, 2015). High-intensity physical exercise condition and Brain Age video game condition might show a better improvement in reaction time at the Stroop task than their respective control condition, low intensity and Tetris, respectively. Regarding the brain activation in older adults, acute intervention with high-intensity physical engenders increases in activation of DLPFC, VLPFC, and FPA compared to low-intensity physical exercise. Activation of R-FPA correlates with the performance (inversely with reaction time) at the Stroop task. For video gaming, this might be the first study to reveal differences in brain activity after an acute intervention with Brain Age or Tetris.

This study is designed to yield insight into the alteration of executive function and its related brain activity because of an acute intervention with a combination of physical exercise and video gaming in older people. The protocol might not be implementable in daily life to improve cognitive abilities. However, the results can support future studies that investigate cognition and the combination of physical exercise and video gaming as well as implications for real life.

